### Laboratory analysis

Nasal tissue samples will be prepared on ice. Protein will be extracted using a small sterile stainless-steel bead within 2.0ml DNA LoBind® tubes (Eppendorf, Hamburg, Germany) which are pre-incubated for 15 minutes on ice. After addition of the nasal tissue sample, the tube will remain on ice for another 15 minutes. According to tissue sample volume, 0.1 to 1ml of buffer solution will be added, consisting of T-PER™ Tissue Protein Extraction Reagent (Thermofisher Scientific, Massachusetts, United States) and cOmplete™ Mini EDTA-free Protease Inhibitor Cocktail (Roche, Basel, Switzerland), in a proportion of 1 tablet for 10 ml of T-PER buffer. Tissue samples will then be placed in a homogeniser at 50Hz for at least 7 minutes and then centrifuged for 10 minutes at 4000rpm at 4°C. The supernatant will then be extracted into clean LoBind® tubes and stored at -80°C prior to analysis. A Pierce™ bicinchoninic acid (BCA) protein assay (Thermofisher Scientific, Massachusetts, United States) will be run on an aliquot of each sample in duplicate to determine protein volumes.

Processed nasal tissue samples will be analysed in duplicate with multiplex detection via electrochemiluminescence, using the MESO QuickPlex SQ 120 (Meso Scale Diagnostics, Maryland, United States). R-PLEX assays for IgE and periostin will be used alongside a custom U-PLEX assay for ENA-78, eotaxin, eotaxin-2, G-CSF, IFN-β, IFN-γ, IL-1β, IL-2, IL-4, IL-5, IL-6, IL-8, IL-9, IL-10, IL-12p70, IL-13, IL-15, IL-17A, IL-22, IL-23, IL17E/IL25, IL-33, MCP-1, MCP-4, MIP-1α, MIP-3α, TNF-α, TSLP, VEGF-A and BAFF. 50–100μg of protein per sample will be used for each assay.

Microbiome analysis for nasal bacteriology swabs would be undertaken in conjunction with a bioinformatics team at the Quadram Institute Bioscience in Norwich. The LotuS2 pipeline developed in this group will be used to analyse these samples, having demonstrated that this pipeline produces more accurate microbiome reconstructions than contemporary pipelines [7]. Due to these samples likely being relatively low bacterial–high human biomass (compared to other environments), special care will be taken to avoid human contaminants using a technique developed in this group [8].

### Outcome measures

The primary outcome measure will be mean expression for each cytokine listed within a core set of biomarkers for treatment responder and non-responder groups. Responders will be defined as participants with a minimum 10-point improvement from their baseline SNOT-22 score at 6 months from randomisation to the MACRO trial. The cytokine data and microbiome profiles will be linked with the MACRO trial data from the Oxford Surgical Intervention Trials Unit following completion of the MACRO trial. MACRO data includes participant demographic information, disease-specific health-related quality of life using the SNOT-22 at 6 months, endoscopic Lund–Kennedy score, Lildholdt polyp grading score, health-related quality of life and quality-adjusted life-years using the SF-12v2 and EQ-5D-5 L questionnaires, olfactory function measured using Sniffin’ Sticks, and health-care resource use recorded using patient questionnaires.

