### Participants

All participants are recruited from existing MACRO trial and are subject to the full eligibility criteria detailed in the MACRO protocol [6]. Selected eligibility criteria include:

Adults aged 18 and over with a minimum of 12 weeks’ history of inflammation of the nose and paranasal sinuses characterised by two or more symptoms, one of which should be either (1) nasal blockage, obstruction or congestion or (2) nasal discharge (anterior or posterior nasal drip). Other symptoms may include facial pain or pressure and reduction or loss of smell.Moderate or severe symptoms within the last 3 months with a SNOT-22 score ≥ 20.Symptom control not achieved following previous alternative medical therapy, including intranasal corticosteroids, short courses of antibiotics, or saline rinses, and therefore considered eligible for ESS.

Participants will be excluded if they meet any of the following criteria or those detailed in the full MACRO trial protocol:

Lund–Mackay non-contrast CT scan score < 4.Macrolide antibiotic treatment for >3 continuous weeks within the last 12 months.ESS in the previous 6 months or visible, open sinus cavities from previous surgery.Taking maintenance oral steroids or biologicsHas received systemic corticosteroids in the last one month.Rare or complex sinus conditions, such as CRS secondary to systemic disease (e.g. ciliary dyskinesias or granulomatous diseases) or suspected malignancy.Allergic fungal rhinosinusitis confirmed or suspected on CT imaging necessitating immediate surgery.Severe asthma (taking high doses of inhaled steroids, i.e. >1.5 mg per day).

All participants will have received nasal endoscopy within 3 months prior to recruitment to confirm CRS phenotype, and a non-contrast CT scan within 18 months prior to recruitment to confirm suitability for ESS.

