### Recruitment

Participants will be recruited from January 2019 to September 2023 from participating UK sites. The recruitment target will be 120 patients in total across all three arms of the MACRO trial; equating to approximately 40 participants per arm. An a-priori sample size calculation was not possible due to lack of information around the baseline prevalence and variance of each cytokine included within the study groups and the likely difference between groups.

Patients will be approached for recruitment to ExpRess following randomisation to any of the three MACRO trial arms of surgery, macrolide antibiotics or placebo. Patients will be approached in clinic by the principal investigator or the research nurse and will be given a recruitment pack that will include a participant information sheet (S1 File) and consent forms. Following written informed consent, patients will have nasal tissue samples and endoscopically guided nasal swabs collected either at the point of randomisation or at their 6 month follow up visit. Participants randomised to the surgical arm of the MACRO trial are also eligible to have samples collected at the time of surgery instead, which is within 6 weeks of randomisation. This process is outlined in Fig 1.

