### Statistical analysis

Data will be analysed using RStudio version 1.2.13 software (RStudio, Massachusetts, United States). For continuous variables, results will be expressed as mean and standard deviation. Data distribution will be tested for normality using a Shapiro-Wilk test. If the variables are not normally distributed, the following statistical tests will be used: for dichotomous variables, a chi-square test will be used to determine difference between groups; while, for continuous variables, a Kruskal-Wallis test will be used for between-group comparison. If expression levels of biomarkers are below the detection limit, they will be replaced by the value 0 for analysis purposes. A p-value of <0.05 is considered significant.

For objective 1 the expression of each cytokine will be expressed as mean and standard deviation for participants from each MACRO trial arm. For objective 2 each MACRO trial arm will be analysed separately. Logistic regression analysis will be performed to determine the impact of cytokine expression levels on binary responder status (defined as a minimum 10-point improvement in baselines SNOT-22 score at 6 months). For objective 3 logistic regression analysis will be performed to determine the impact of cytokine expression levels on phenotypic characteristics such as the presence of nasal polyps or raised total serum IgE (>100 IU/ml). For objective 4 microbiome profiles will be reported as mean distribution of bacterial strains. Bacterial profiles will be compared alongside outcomes from the MACRO trial database using univariate and multivariate statistics, associating microbiome profiles to cytokine profiles and treatment success on included patients.

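### The score-only responder rule, modelled within each arm, would label ESS-arm participants who had no surgery, and participants who improved after off-arm treatment, as responders or non-responders to that arm

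*Protocol article*

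**What the plan says.** The primary outcome is mean cytokine expression in responders and non-responders. Under Outcome measures, "Responders will be defined as participants with a minimum 10-point improvement from their baseline SNOT-22 score at 6 months from randomisation". The Statistical analysis section repeats the rule for the logistic model, as "binary responder status (defined as a minimum 10-point improvement in baselines SNOT-22 score at 6 months". Neither statement has a condition on treatment received.

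The model is run arm by arm: "For objective 2 each MACRO trial arm will be analysed separately". This sentence does not say whether arm means as randomised or as treated, although the Abstract and the Recruitment section describe the arms by randomisation.

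Three other statements bear on the point:

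- Recruitment: patients are approached after randomisation. Tissue may be taken at randomisation or at the 6-month visit, and ESS-arm participants may instead give it at surgery, which is described as taking place within 6 weeks of randomisation. Having had surgery is not a condition for giving a sample.
- Participants: "Symptom control not achieved following previous alternative medical therapy" is an entry criterion, and everyone is considered eligible for ESS.
- Outcome measures: the linked MACRO data include "health-care resource use recorded using patient questionnaires". No role is given to these data in the responder rule.

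**The concern.** The Introduction and Discussion set out the purpose: to find biomarker clusters that separate responders from non-responders, as groundwork for predicting who responds to medical or surgical therapy. For that purpose the label should say something about the treatment whose name the model carries. A score-only label credits the arm with whatever happened in the 6 months.

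Two cases follow from the text as written. An ESS-arm participant whose operation had not taken place by the 6-month score can still have a tissue sample, and would enter the surgery model as a surgical responder or non-responder. A clarithromycin or placebo participant who gains 10 points after off-arm surgery, systemic corticosteroids or additional antibiotics would enter as a responder to clarithromycin or placebo.

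If off-arm treatment goes mainly to those doing poorly, participants who did not respond to their arm move into its responder group and real marker differences are diluted. If the choice of that treatment follows phenotype, a marker of the phenotype could look like a predictor of response to the arm. With about 40 participants per arm, a handful of such labels would matter.

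**Working it through.** **The plan's own figure.** "The recruitment target will be 120 patients in total across all three arms of the MACRO trial", "equating to approximately 40 participants per arm": 120 / 3 = 40, which reproduces. The article states no effect size, SD, power, responder share or rate of off-arm treatment or missed surgery. Everything below except the 40 and the 0.05 threshold ("A p-value of <0.05 is considered significant", taken as two-sided) is an assumption.

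**A. Participants whose label carries no information on the arm's treatment** (for example, ESS-arm participants without surgery). Let a fraction c of the arm be of this kind, with a label unrelated to the marker. The apparent responder/non-responder difference is then (1 − c) × d. A comparison of two means stands in for the planned logistic regression:

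power = Φ( difference / √(1/n₁ + 1/n₀) − 1.96 ), in SD units.

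Take d = 0.8 SD and half the arm responding (20 v 20).

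- c = 0: 0.8 / √(1/20 + 1/20) = 0.8 / 0.316 = 2.53; Φ(0.57) = 0.716.
- c = 10%, all kept: 0.72 / 0.316 = 2.28; Φ(0.32) = 0.624.
- c = 10%, left out (18 v 18): 0.8 / 0.333 = 2.40; Φ(0.44) = 0.670.

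| c (participants of 40) | Apparent difference if kept | Power if kept | Power if left out |
|---|---|---|---|
| 0 | 0.80 SD | 0.716 | 0.716 |
| 5% (2) | 0.76 SD | 0.671 | 0.694 |
| 10% (4) | 0.72 SD | 0.624 | 0.670 |
| 20% (8) | 0.64 SD | 0.525 | 0.619 |
| 30% (12) | 0.56 SD | 0.425 | 0.562 |

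With 70% responding, power if kept falls from 0.640 at c = 0 to 0.550 at 10% and 0.458 at 20%; leaving those participants out gives 0.595 and 0.545. If nobody is affected, leaving them out changes nothing.

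**B. Non-responders who improve after off-arm treatment.** Assume 40% true responders, 10% to 30% of non-responders treated off-arm, and 50% to 70% of those then gaining 10 points.

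- False responders: 40 × 0.6 × 0.10 × 0.50 = 1.2, up to 40 × 0.6 × 0.30 × 0.70 = 5.0.
- The difference is multiplied by 0.4 / (0.4 + false responders / 40). At the low end this is 0.4 / 0.430 = 0.93 (7% smaller); at the high end, 0.4 / 0.526 = 0.76 (24% smaller).
- Simulated t-tests with d = 0.9 SD and 60% of those treated improving give power of about 76%, 69%, 62% and 55% when 0, 10, 20 and 30% of non-responders are treated off-arm.

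**C. Would relabelling everyone with off-arm treatment as a non-responder be better?** Use the set-up of B with 20% of non-responders treated off-arm, and let some true responders also have had such a course. The score-only rule then has about 62% to 63% power.

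| True responders who also had a course | Power under relabelling |
|---|---|
| 10% | 69% |
| 15% | 63% |
| 20% | 60% |
| 30% | 51% |

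Relabelling gains when few true responders had a course, breaks even near 15% and loses above that.

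**The case against.** The strongest reply is that nothing here is misstated. A 6-month score from randomisation, analysed by arm, is a treatment-policy definition using the instrument and time point of MACRO's primary outcome. Asking which biomarkers accompany improvement under each allocated strategy is a legitimate question. Participants also fall under the MACRO protocol, which is not shown and may restrict or record off-arm treatment. The only timing given for surgery, within 6 weeks, speaks against many missed operations.

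Much of this stands. A reader might infer that response biomarkers in this study are in fact misattributed. The article does not support that: it reports no rescue treatment, crossover or missed surgery, and moving from prior treatment failure and eligibility for ESS to off-arm treatment within 6 months is conjecture. A reader might also infer that anyone with off-arm treatment should be made a non-responder in the primary model. Part C of the working shows that this trades one labelling error for another, with an unknown balance. It would also need care in the ESS arm, where a course given around surgery may belong to the surgical pathway.

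The reply does not dispose of the narrower point. The rule is ExpRess's own, stated twice and tied to its primary outcome, so it is not a detail left for another document. The usual reason for keeping everyone under their allocation is to protect a randomised comparison, and a within-arm model of responders against non-responders has none. A person who was not operated on cannot show which biomarkers go with response to an operation.

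**Conclusion.** The point holds in a limited form. As written, the rule would score unoperated ESS-arm participants, and participants who improved after off-arm treatment, as responders or non-responders to their arm. That fits poorly with the aim of finding biomarkers of response to a treatment. How often this happens cannot be known from the article.

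On the assumptions in part A (0.8 SD, half responding, labels of affected participants unrelated to the marker), each 10% of an arm affected removes 10% of the apparent marker difference. Power falls by about 9 points at 10% affected (71.6% to 62.4%) and about 19 at 20% (71.6% to 52.5%). These figures are for a single marker at 0.05 under a normal approximation; they show sensitivity and are not an estimate for this study.

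The case is firm for leaving unoperated participants out of the surgery-response model, because this helps if there are any and changes nothing if there are none. It is not firm for replacing the score-only definition in the clarithromycin and placebo arms.

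**What to change.** For objective 2:

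1. State that arms are as randomised.
2. In the ESS arm, leave participants who had no ESS before the 6-month score out of the surgery-response model. Report how many were left out, and give the all-randomised version alongside.
3. In the clarithromycin and placebo arms, keep the 10-point score-only definition as primary.
4. Add a sensitivity analysis that sets aside participants whose linked MACRO data show off-arm ESS, systemic corticosteroids or non-trial antibiotics for CRS before the 6-month score. Set them aside; do not relabel them as non-responders.

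The cost is a wording change, a treatment-received variable and a little more analysis, all before the label is derived at linkage. There are two downsides. A few participants are lost from models that are already small, and the surgery-response result then describes those operated on, not everyone allocated to surgery. The changes also depend on how well the linked data record treatment type and timing: the article mentions resource-use questionnaires but does not say that they capture drug class, indication or dates, so this should be checked first. No change to patient care is proposed.

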The primary outcome measure for the MACRO trial is the sino-nasal outcome test-22 (SNOT-22) score at 6 months after randomisation. Secondary outcomes include the endoscopic Lund–Kennedy score, olfactory function measured using Sniffin’ Sticks, and health-care resource use. The parallel ExpRess study involves collection of nasal tissue samples and bacterial swabs from MACRO trial participants. The ExpRess study aims to correlate CRS endotypes with clinical parameters from the ongoing MACRO trial, including olfactory function and outcomes in terms of response to treatment using core biomarkers sets. This will further refine the biomarker sets that could be utilised in future clinical practice for personalised treatment for CRS.

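### Objective 2 rests on a 10-point SNOT-22 responder flag with no stated baseline adjustment, which loses power at about 40 per arm and can mix baseline severity with response

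*Protocol article*

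**What the plan says.** The Outcome measures section sets the primary outcome: "The primary outcome measure will be mean expression for each cytokine listed within a core set of biomarkers for treatment responder and non-responder groups". It then defines the groups: "Responders will be defined as participants with a minimum 10-point improvement from their baseline SNOT-22 score at 6 months from randomisation".

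The Statistical analysis section carries the flag into objective 2: "Logistic regression analysis will be performed to determine the impact of cytokine expression levels on binary responder status". It also states "For objective 2 each MACRO trial arm will be analysed separately". The Recruitment section gives a target of 120, "equating to approximately 40 participants per arm". For continuous variables that are not normally distributed, "a Kruskal-Wallis test will be used for between-group comparison".

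Baseline SNOT-22 appears only inside the definition of the flag. It is not named as a covariate, and the text does not say that the logistic model is unadjusted.

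The continuous score is available. The Introduction says "The primary outcome measure for the MACRO trial is the sino-nasal outcome test-22 (SNOT-22) score at 6 months after randomisation", and the Outcome measures section lists SNOT-22 at 6 months among the data to be linked. Baseline SNOT-22 must be held as well, or the flag could not be computed. Entry requires "Moderate or severe symptoms within the last 3 months with a SNOT-22 score" of 20 or more, and the criteria listed in the article set no upper limit.

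**The concern.** Two separate problems follow from leading with this flag.

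**Lost information.** A graded outcome is cut at one point, so someone who improves by 11 points counts the same as someone who improves by 40. With about 40 participants per analysis and no sample-size calculation, the study has little power to spare.

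**Baseline severity.** A raw 10-point fall is 10/20 = 50% of the score for a participant entering at 20, but 10/70 = 14% for one entering at 70. If 6-month SNOT-22 rises by less than one point per baseline point (regression to the mean), participants with high baselines cross the line more often. A cytokine that mainly marks baseline severity can then differ between responders and non-responders while saying nothing about outcome beyond severity. That matters because the study aims to find biomarkers that separate the two groups, and the plan describes the model as showing the impact of cytokine levels on response.

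**Working it through.** **The plan's own figures.** 120/3 = 40 per arm, which agrees with the Recruitment section. No power, effect size or SD is given, so there is no power figure to reproduce.

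**Inputs from the documents.** n = 40 per analysis; entry at SNOT-22 of 20 or more; cut-off of 10 points; significance level 0.05 (two-sided assumed).

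**Inputs that are assumptions.** The documents give no SNOT-22 SD, slope, response rate or marker-baseline correlation. Two sets were simulated, both with residual SD 17:
- Set A: baseline N(45, 18) cut at 20; mean improvement 12 points; about 54% responders.
- Set B: baseline N(45, 20) truncated to 20-110 (realised mean 49.0, SD 16.7); mean improvement 10 to 20 points.

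**Model (set B form).** 6-month score = 49.5 − mean improvement + slope × (baseline − 49.5) − effect × marker + N(0, 17). The marker is in SD units. The flag is 1 if baseline minus 6-month score is at least 10.

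**Step 1: chance of response by baseline, with no marker effect.** P = 1 − Φ((10 − expected improvement)/17), with mean improvement 15 and slope 0.5.
- Baseline 20: expected 6-month score 34.5 + 0.5 × (20 − 49.5) = 19.75; improvement 0.25; P = 1 − Φ(9.75/17) = 0.28.
- Baseline 70: expected 6-month score 34.5 + 0.5 × (70 − 49.5) = 44.75; improvement 25.25; P = 1 − Φ(−15.25/17) = 0.82.
- At slope 1.0, P is 0.62 at every baseline, so the mechanism disappears.

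**Step 2: power at n = 40, slope 0.5, marker unrelated to baseline.**

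| Set | Effect per marker SD | Flag, unadjusted logistic | 6-month SNOT-22 adjusted for baseline |
|---|---|---|---|
| A | 5 points | 22% | 42% |
| A | 7 points | 40% | 69% |
| B | 5 points | 25-26% | 40-42% |
| B | 8 points | 51-52% | 79% |
| B | 10 points | 67-71% | 92% |

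The gap in set A is 69 − 40 = 29 percentage points at an effect of 7, and 42 − 22 = 20 at an effect of 5. Adding baseline to the logistic model recovers little: 43% at 7 points (set A) and 56% at 8 points (set B). Most of the loss therefore comes from dichotomising.

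**Step 3: rejection rate at n = 40 for a marker linked to outcome only through baseline (unadjusted logistic).**

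| Set | Slope | Correlation 0.3 | 0.5 | 0.7 |
|---|---|---|---|---|
| A | 0.5 | 7-8% | 14-16% | not run |
| A | 0.8 | 5% | 6% | not run |
| A | 1.0 | 4% | 5% | not run |
| B | 0.3 | 14% | 30% | 56% |
| B | 0.5 | 12% | 22% | 34% |
| B | 0.7 | 8% | 10% | 17% |
| B | 1.0 | 5% | 5% | 7% |

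Kruskal-Wallis at slope 0.5 and correlation 0.5 rejects 16% (A) and 18% (B). In set B, adding baseline to the logistic model brings the rates to about 5-7%, and the baseline-adjusted linear model gives about 4-6%.

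**Simulation error.** With 1,500 runs the standard error near 50% is √(0.25/1500) = 1.3 points. With 1,000 runs near 5% it is √(0.05 × 0.95/1000) = 0.7 points.

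**The case against.** **The article is condensed and a fuller analysis plan may list covariates.** This stands for the logistic model: naming no covariate is not the same as ruling one out. It does not remove the point. The group means and Kruskal-Wallis take no covariate by construction, and the dichotomy is an affirmative choice stated in two sections.

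**Continuous outcomes are not ignored.** The Abstract announces correlations between biomarkers and parent-trial outcomes, including improvement in quality of life. That is fair, so the flag should not be called the study's only inferential outcome. But the Abstract does not name SNOT-22 for this purpose or mention baseline adjustment, the Statistical analysis section does not develop it for objective 2, and a correlation with change depends on baseline in the same way.

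**Objective 2 asks whether cytokines differ between responders and non-responders.** If a severity-linked cytokine does differ, rejecting that null hypothesis is correct. This stands. A reader might infer that the plan inflates the type I error of its primary comparison. It does not in the strict sense: the fault is confounding by severity of the reading that the cytokine affects response.

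**The size depends on assumptions.** This also stands. A reader might infer that any marker of severity will look predictive. The association needs a slope below 1 and a clear correlation with baseline. Rejection rates for the pooled 120 would be larger, but they do not describe a plan that analyses arms separately.

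**Sampling time.** The Recruitment section allows tissue at randomisation, at surgery or at the 6-month visit. For 6-month tissue the correlation with baseline severity is unknown, and no choice of outcome model turns such a sample into a predictor.

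**Conclusion.** The point holds and is worth correcting. The power loss is the firmer part: it appears in every scenario run and does not need a marker-baseline correlation. At n = 40 it is about 20 percentage points at 5 points per marker SD and 29 at 7 points in set A. The exact values rest on the assumed SDs and slope.

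The baseline-severity part is conditional. At n = 40, with slope 0.5 and correlation 0.5, the unadjusted flag model rejects about 14-22% of the time for a marker that adds nothing beyond severity. This falls to about 5% as the slope approaches 1. At correlation 0.3 and slope 0.5 it is 7-12%. The documents do not show where the real slope or correlations lie, so the direction is secure only for a slope below 1 and the size is open.

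**What to change.** In the Statistical analysis section, for objective 2 and within each arm:
- Make a linear regression of 6-month SNOT-22 on the biomarker, adjusted for baseline SNOT-22, the main inferential model.
- Keep the 10-point responder comparison as a supportive analysis, with baseline SNOT-22 added to the logistic model.
- State that unadjusted means in responders and non-responders, and any Kruskal-Wallis test on them, are descriptive.
- State that results from tissue taken at the 6-month visit are not evidence of prediction under either model.

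The cost is wording only, because both scores come with the linked parent-trial data. The small downside is that the responder contrast, which is easy to communicate clinically, no longer leads the inference. The primary outcome wording would need to be brought into line.
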